## Abstract

**Background:**

Chronic obstructive pulmonary disease (COPD) is a common respiratory disease and the third leading cause of death worldwide. Previous evidence has shown that acupuncture may be an effective complementary alternative therapy for stable COPD. However, large-sample, rigorously designed long-term follow-up studies still need to be completed. Notably, the relationship between the frequency of acupuncture and clinical efficacy in studies on acupuncture for stable COPD still needs further validation. This study aims to evaluate the efficacy and safety of acupuncture for stable COPD and further investigate the dose–effect relationship of acupuncture.

**Methods/design:**

This is a multicenter, randomized, controlled trial that uses central randomization to randomly allocate 550 participants in a 1:1:1:1:1 ratio to once a week acupuncture group, twice a week acupuncture group, three times a week acupuncture group, sham acupuncture group and waiting-list control group. The sham acupuncture group will receive placebo acupuncture treatments three times per week, and the waiting-list control group will not receive any form of acupuncture intervention. The study consists of a 2-week baseline, 12-week of treatment, and 52-week of follow-up. Patients with COPD between 40 to 80 years old who have received stable Western medication within the previous 3 months and have had at least 1 moderate or severe acute exacerbation within the past 1 year will be included in the study. Basic treatment will remain the same for all participants. The primary outcome is the proportion of responders at week 12. Secondary outcomes include the proportion of responders at week 64, change in the St. George's Respiratory Questionnaire (SGRQ) Scale, change in the Modified-Medical Research Council (mMRC) Scale, change in the COPD Assessment Test (CAT) Scale, change in the Lung Function Screening Indicators (LFSI), change in the 6-min walk distance (6-MWD), change in Short-Form 36 Health Survey (SF-36) Scale, the number of moderate and severe acute exacerbations and adverse event rate during the follow-up period.

**Discussion:**

This study will provide robust evidence on whether acupuncture is safe and effective for treating stable COPD. Meanwhile, comparing the differences in efficacy between different acupuncture frequencies will further promote the optimization of acupuncture for stable COPD.

**Trial registration:**

This study was registered in the Chinese Clinical Trial Registry (ChiCTR2200058757), on April 16, 2022.

**Supplementary Information:**

The online version contains supplementary material available at 10.1186/s12906-024-04412-6.

## Introduction

Chronic obstructive pulmonary disease (COPD), characterized by airflow limitation and persistent respiratory symptoms caused by a combination of small airway disease (obstructive bronchitis) and lung parenchymal destruction (emphysema), is the third most common cause of death [1, 2]. In 2019, 212.3 million prevalent cases of COPD were reported globally, including 3.3 million deaths and 74.4 million disability-adjusted life years [3, 4]. Continued exposure to COPD risk factors and an aging population have made COPD a global public health challenge [5]_._ Clinical treatment of stable COPD aims to reduce symptoms, decrease the frequency and severity of acute exacerbations, improve health status, and enhance exercise tolerance. Despite the importance of bronchodilators, glucocorticoids, mucolytics, and antibiotics as clinically indicated drugs in treating stable COPD, there are inevitable side effects [6]. For example, beta_2_-agonists may cause hypokalemia and tardive dyskinesia [7, 8], antimuscarinic drugs cause dry mouth [9], glucocorticoids increase the incidence of pneumonia [10], and antibiotics cause bacterial resistance and tinnitus [11]. Moreover, some patients still have symptoms that cannot be effectively controlled based on conventional medications. Therefore, it is imperative to explore new treatment options that are safe and effective, with fewer side effects, to improve patient symptoms further, reduce acute exacerbations, and minimize the side effects of conventional drug therapy.

Acupuncture has been widely used worldwide as an essential complementary alternative therapy for preventing and treating many chronic diseases. Previous studies have shown that the Borg scale after the 6-min walk test (6-MWT) was significantly better in the acupuncture group than in the control group (treatment as usual). That 6-min walk distance (6-MWD), oxygen saturation, and lung function also improved compared to the control group [12, 13]. Compared with the placebo acupuncture group, the Borg scale score, 6-MWD, pulmonary ventilation function, and St George's Respiratory Questionnaire (SGRQ) were significantly improved in the acupuncture group, and the body mass index (BMI), airflow obstruction, dyspnea, and exercise capacity (BODE) index also experienced improvement [14–17]. The above studies have shown that acupuncture helps to reduce dyspnea, improve exercise capacity, and improve lung function and nutritional status in patients with stable COPD. Systematic reviews based on evidence-based medicine have also demonstrated acupuncture as an effective adjunctive non-pharmacological treatment to improve the quality of life and dyspnea in COPD medically treated patients. However, there still needs to be high-quality randomized controlled trials to validate it [18, 19].

Acupuncture dose affects the acupuncture effect and determines the treatment and prognosis of the disease [20]. Among these, the frequency of acupuncture is essential in influencing the outcome and determining the cost of medical care. However, the relationship between acupuncture frequency and efficacy remains largely unexplored. A recent systematic review found that 36 acupuncture treatments had the best clinical response in patients with major depression compared to 24 and 12 treatments [21]. Previous clinical studies on acupuncture for stable COPD had a treatment frequency of 1–3 times per week, with a treatment period of 2–12 weeks and a total number of sessions ranging from 6–24 [12, 14–17, 22–24]. No clinical studies comparing different frequencies of acupuncture for stable COPD are available; thus, it is not possible to determine the preferred frequency and intervention period for acupuncture for COPD.

Therefore, this study designed a multi-centered, large-sample randomized controlled trial with the aim of (1) evaluate the efficacy and safety of acupuncture for stable COPD and (2) exploring the frequency of acupuncture suitable for stable COPD.

## Methods

### Study design

This study outlines a protocol for a prospective, multicenter, randomized controlled trial in which participants will be assigned to 5 parallel groups. The protocol reporting follows the SPIRIT statement [25], and future trials will follow the Consolidated Standards of Reporting Trials (CONSORT) guidelines [26], including an extension of the Revised Standards for Reporting Interventions in Clinical Trials of Acupuncture (STRICTA) [27].

550 participants with stable COPD who meet the diagnostic criteria will be enrolled in this study. All participants are coming from 11 tertiary hospitals in Sichuan Province, China: Hospital of Chengdu University of TCM, Sichuan Provincial People's Hospital, Chengdu First People's Hospital, Chengdu Second People's Hospital, Chinese Traditional Medicine Hospital of Meishan, Mianyang Hospital of Traditional Chinese Medicine, Deyang People's Hospital, Guangyuan Hospital of Traditional Chinese Medicine, Panzhihua Integrated TCM and Western Medicine Hospital, Meishan People's Hospital, and Chengdu TCM Hospital of Pidu District. The entire study period consists of 2 weeks of baseline, 12 weeks of treatment, and 52 weeks of follow-up. A flow chart of the trial design is shown in Fig. 1, and patient enrollment, intervention, and assessment times are shown in Table 1.

**Fig. 1 Fig1:**
[figure not shown]
Research flow chart

**Table 1 Tab1:**
[figure not shown]
Timepoint for recruitment, interventions and evaluation

*SGRQ *St. George's Respiratory Questionnaire, *mMRC *Modified-Medical Research Council, *CAT *COPD Assessment Test, *6-MWD *6-min walk distance, *SF-36 *Short-Form 36 Health Survey

### Randomization and blinding

The central randomization system is used to conduct dynamic block group randomization stratified by center, and participants are randomly assigned in a ratio of 1:1:1:1:1 to once a week acupuncture group, twice a week acupuncture group, three times a week acupuncture group, sham-acupuncture group, and waiting-list control group. Beijing Bioknow Information Technology Co. will perform randomization. An independent researcher from each center not involved in treatment and outcome assessment is responsible for logging on to the central randomization system and entering randomization information (including the center number and the participant's name in *pinyin* initials). Randomization numbers and group assignments will be emailed to this independent assessor. Patients will be settled in separate treatment rooms to avoid communication with each other. Evaluators, statisticians, and participants will be blind to treatment allocations. The location of acupoints and the use of assistive devices will be the same for the acupuncture and sham acupuncture groups.

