### Patient recruitment

Recruitment strategies include poster recruitment, community recruitment, online recruitment, respiratory outpatients, and previous inpatients. Patients will be informed of study specifics, including study purpose, subgroup status, interventions, treatment period, benefits, and potential risks. A respiratory specialist will diagnose patients who agree to participate in this study and must sign an informed consent form before randomization to the group. All patient information will be kept confidential. Patients may withdraw at any trial stage, and the reasons for patient withdrawal will be well documented.

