### Manual acupuncture (MA) group

There are 3 acupuncture groups, which include once a week acupuncture group, twice a week acupuncture group and three times a week acupuncture group. The patient remains prone during acupuncture, and a soft pillow is placed on the front of the patient's chest to elevate the front of the chest to facilitate needling. The acupuncturist will sterilize the skin around the acupoint using 75% alcohol, then attach a rubber base to the acupoint and insert the needle through the rubber base into the acupoint. For LU1, a 1 cun needle (0.25 × 25 mm, Suzhou Hua Tuo, China) is used, and the needle is inserted in a lateral direction for approximately 15–20 mm. The needle is angled at 45° toward the spine for the dorsal acupoints. BL13 is inserted with a 0.5 cun needle (0.25 × 13 mm, Suzhou Hua Tuo, China) for approximately 5–10 mm. EX-B1 and BL20 are inserted with a 1 cun needle (0.25 × 25 mm, Suzhou Hua Tuo, China) for approximately 15–20 mm. BL23, ST36, and ST40, using a 1.5-inch needle (0.25 × 40 mm, Suzhou Huatuo, China), are inserted for approximately 25- 30 mm. After piercing the needle, gentle lifting, thrusting, swirling, and rotating movements are performed on the needle body to achieve *deqi* sensation (soreness, numbness, distension, or heaviness) [30]. The patient's degree of *deqi* sensation will be assessed immediately after the patient has *deqi* sensation [31]. The needles will be retained for 30 min each time, and *deqi* sensation operation will be performed every 10 min, about 15 s each time. When removing the needle, the acupuncturist uses a dry, sterilized cotton ball to gently press the needled area to avoid bleeding.

Once a week acupuncture group: needling once a week with 6-day intervals, 12 times for 12 weeks. Twice a week acupuncture group: 2 needling sessions per week, with a 3-day interval between needling sessions, for 24 needling sessions over 12 weeks. Three times a week acupuncture group: 3 times a week with 1-day intervals for 36 needling sessions over 12 weeks.

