### Sham acupuncture (SA) group

The SA group will receive placebo acupuncture in bilateral LU1、EX-B1、BL13、BL20、BL23、ST3, and ST40 on a treatment protocol similar to the acupuncture group. The frequency of the SA treatment is three times a week, with a one-day interval between each treatment, for a total of 36 treatments over 12 weeks. After routine skin disinfection, a rubber soft pad is adhered to the acupoint. A disposable blunt needle (0.3 × 0.13 mm) is used to pierce the base of the rubber soft pad so that the needle body is fixed vertically on the patient's skin. The patient will feel pain but without puncturing the skin. The treatment is simulated by twisting, turning, lifting, and inserting manipulation every 10 min during the treatment, gently swinging the needle body, but without producing a *deqi* sensation. The needles are left for 30 min. Considering the ethical requirements, a free compensatory acupuncture treatment will be given at the end of the trial (Fig. 3).

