### Waiting-list control group

No change in the original primary treatment of COPD patients and no acupuncture intervention will be given. Patients will be required to complete the appropriate tests and scale assessments at the appropriate time points and be given free acupuncture treatment at the end of the trial.

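### The protocol says participants are blind to allocation, but 7 of the 10 pairwise arm contrasts cannot be participant-blind, and the primary outcome is patient-reported

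*Protocol article*

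**What the plan says.** Randomization and blinding allocates participants 1:1:1:1:1 to five arms and then states, without exception: "Evaluators, statisticians, and participants will be blind to treatment allocations". The same section adds separate treatment rooms, and the same acupoints and devices for real and sham needling.

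The arms are described as follows.

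- Waiting list: the abstract says "the waiting-list control group will not receive any form of acupuncture intervention", and the arm's own section says "No change in the original primary treatment of COPD patients and no acupuncture intervention will be given".
- Real acupuncture, lower frequencies: "needling once a week with 6-day intervals, 12 times for 12 weeks" and "2 needling sessions per week, with a 3-day interval between needling sessions" (24 sessions in all). The third real arm has 36 sessions, three a week.
- Sham: "The frequency of the SA treatment is three times a week", also 36 sessions. There is no sham at the lower frequencies.

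On what participants know beforehand, Patient recruitment says: "Patients will be informed of study specifics, including study purpose, subgroup status, interventions".

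The primary outcome is the week-12 proportion of responders, meaning a fall of at least 4 units in the SGRQ total score. The Discussion describes the SGRQ as a quality-of-life questionnaire. Its limitations paragraph names only the acupuncturist as impossible to blind.

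**The concern.** The sentence claims for all five arms a property that the design can offer to only some of them. Nothing elsewhere in the article withdraws it, and the limitations paragraph, where a correction would be expected, is silent about participants.

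The stakes lie in how results will be read. Where participants know what they are getting, a difference in a patient-reported responder rate mixes any effect of needling with expectation, disappointment and the effect of more frequent contact. Two comparisons central to the stated aims are affected: acupuncture versus no acupuncture, and one frequency versus another. A report that repeats the blinding sentence would give those comparisons the standing of the real-versus-sham comparison at equal frequency.

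**Working it through.** **Step 1. The plan's own figure.** Sample size calculation gives mean SGRQ changes of -7.1 (three times weekly), -2 (sham) and -0.8 (blank control), SD 14.2, two-sided 5% error and 80% power. A one-way ANOVA on these three means (noncentral F) has power 79.6% at 87 per group and 80.1% at 88, so the stated 88 reproduces. Then 88 / (1 - 0.20) = 110, and 5 × 110 = 550. The blinding point does not depend on this figure. It does show that 2 of the 3 pairs among the arms used for sizing involve the waiting list.

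**Step 2. Count the contrasts.** Five arms give 5 × 4 / 2 = 10 pairs. Sessions over 12 weeks: once weekly 12, twice weekly 24, three times weekly 36, sham 36, waiting list 0.

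| Type of contrast | Pairs | Sessions | Participant-blind? |
|---|---|---|---|
| Any needled arm v waiting list | 4 | 12, 24, 36 or 36 v 0 | No |
| Between real frequencies | 3 | 12 v 24, 12 v 36, 24 v 36 | No: attendance is known |
| Once or twice weekly v sham | 2 | 12 v 36, 24 v 36 | Depends on what participants know of the sham schedule |
| Three times weekly v sham | 1 | 36 v 36 | Schedule matched; blinding credible |

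So 4 + 3 = 7 of 10 are not participant-blind with no further assumption, and 9 of 10 if the sham schedule is known. Of the 6 contrasts of a real arm with a control, 3 are certainly unmasked, 2 conditionally, and 1 is matched.

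**Step 3. Could it matter on the primary outcome?** Assume normally distributed changes with the plan's SD. The responder probability is Φ((-4 - mean) / 14.2).

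- Three times weekly: Φ(3.1 / 14.2) = 58.6%
- Sham: Φ(-2 / 14.2) = 44.4%
- Blank control: Φ(-3.2 / 14.2) = 41.1%

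The planned gaps are 58.6 - 44.4 = 14.2 points versus sham and 58.6 - 41.1 = 17.5 points versus waiting list.

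The article gives no size for an expectation effect, so take 1 to 4 SGRQ points as an assumed range. Starting from the blank-control mean:

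- 1-point shift: Φ(-2.2 / 14.2) - Φ(-3.2 / 14.2) = 2.8 points
- 4-point shift: Φ(0.8 / 14.2) - Φ(-3.2 / 14.2) = 11.2 points

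From the sham mean the results are almost the same (2.8 and 11.2). This is an illustration of sensitivity, not an estimate of bias.

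**The case against.** The best defence is context. The sentence stands beside a description of separate rooms and identical acupoints and devices, so it is probably about masking real against sham needling. The Discussion calls the no-treatment arm a blank control and promises compensatory treatment to forestall disappointment, so the authors evidently expect those patients to know they receive nothing. Blinding is to be checked by a question at week 12. Data are collected by questioning, by telephone or on site, so blinded evaluators can limit interviewer bias.

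Much of this is fair, but it shows what the sentence should have said. The text names participants without exception, and the limitations do not correct it. Few readers would take a waiting list to be blind; the frequency arms are easier to overlook. The week-12 question may reveal failed masking but does not supply it, and blinding the evaluator leaves the patient's expectation untouched.

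Three stronger readings are tempting and are not supported.

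- A reader might infer that at most 2 × 110 = 220 participants can be blind. That requires once- and twice-weekly participants to know that sham is given only three times a week. Patient recruitment says interventions are explained, not that this detail is disclosed, and the consent text is not shown. Without disclosure, all 4 × 110 = 440 needled participants could be blind to real versus sham.
- A reader might take the sham-versus-blank difference, 1.2 of the 6.3 units between three-times-weekly acupuncture and blank control, as the share due to expectation. The Discussion says the blunt needle may itself stimulate the acupoints, so the difference cannot be read that way.
- A reader might conclude that three-times-weekly versus sham must become the sole primary comparison. That is a separate decision. On means it would need 2 × (1.960 + 0.842)² × 14.2² / 5.1² ≈ 122 per group rather than 88. Correcting a blinding statement does not require it.

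**Conclusion.** The statement is wrong as written. Participants are not blind in 7 of the 10 pairwise contrasts: 4 with the waiting list and 3 between real frequencies. This follows from the arm descriptions alone. For the 2 contrasts of once- or twice-weekly acupuncture with sham, masking of real versus sham is uncertain and depends on what consent discloses; even if it holds, the schedules differ visibly. Three-times-weekly real versus sham is the only schedule-matched contrast and the only one for which participant blinding is credible without further assumption.

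The claimed blinding of evaluators and statisticians is not contradicted. The size of any expectation effect is unknown. The figure of about 3 to 11 responder points rests on normal changes, the plan's SD and an assumed shift of 1 to 4 SGRQ points, and shows only that the effect could be material against the planned gaps.

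**What to change.** 1. In Randomization and blinding, replace the sentence with: *Evaluators and statisticians are blind to allocation; participants in the needled arms are intended to be blind to real versus sham needling but not to session frequency; waiting-list participants are not blind.*
2. Add the same point to the limitations paragraph of the Discussion, next to the acupuncturist.
3. Report waiting-list and between-frequency contrasts as not participant-blind and as including expectation effects.
4. Treat three-times-weekly versus sham as the only schedule-matched blinded contrast when claiming a specific effect of acupuncture.
5. State what consent tells participants about the sham schedule, and label once- or twice-weekly versus sham as potentially unmasked accordingly.

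The cost is a less favourable description of the blinding. No new data are needed, and the sample size does not change.

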### Participants

#### Inclusion criteria

Participants who meet the diagnostic criteria for COPD according to the Global Initiative for COPD and conform to all the following criteria will be included in the study [28]: 1) stable condition without acute exacerbation in the last 4 weeks; 2) age between 40 and 80 years, both sexes; 3) FEV1pre between 25 and 80% after inhaled bronchodilators; 4) at least 1 moderate or severe acute exacerbation within the past year; 5) receiving stable Western medication within the previous 3 months; 6) willing to cooperate with the study and sign an informed consent form.

#### Exclusion criteria

Patients who meet any of the following conditions will be excluded: 1) combination of the severe cardiovascular, neurological, hematological, immune system, and malignant tumor diseases; 2) combined respiratory diseases that significantly impact the study (active tuberculosis, bronchial asthma, severe bronchiectasis, primary pulmonary hypertension, interstitial lung disease); 3) history of segmentectomy, wedge resection, lobectomy, total pneumonectomy, or lung volume reduction (including bronchoscopic lung volume reduction) for COPD; 4) continuous oxygen therapy is required according to long-term oxygen therapy (LTOT) criteria (oxygen therapy duration > 15 h/d) [29]; 5) unable to perform pulmonary function tests, unable to walk independently, unable to cooperate in completing questionnaires; 6) persistent breakage or infection of skin tissue at the needle site, coagulation dysfunction, skin allergy; 7) participated in another clinical trial or performed acupuncture for respiratory disease within the last 3 months; 8) pregnant and lactating women.

### Patient recruitment

Recruitment strategies include poster recruitment, community recruitment, online recruitment, respiratory outpatients, and previous inpatients. Patients will be informed of study specifics, including study purpose, subgroup status, interventions, treatment period, benefits, and potential risks. A respiratory specialist will diagnose patients who agree to participate in this study and must sign an informed consent form before randomization to the group. All patient information will be kept confidential. Patients may withdraw at any trial stage, and the reasons for patient withdrawal will be well documented.

